### Control

In the control group, immunization sessions were conducted as per routine. This meant the vaccination team organized weekly vaccination sessions at health facilities for villages situated <5 km away from the health center and when possible, monthly vaccination sessions in communities situated ≥5 km away.

### Outcomes Assessment

Data to assess effects of the interventions were collected from baseline, midline, and endline surveys. The baseline survey also provided data on population characteristics and child access to EPI vaccination prior to the intervention. Each village was mapped using the “my position” function of the Google Earth smartphone app and divided into clusters of about 30 buildings, assuming that each cluster would have at least 20 children aged 0-59 months (based on a pretest conducted in the area). One cluster was randomly selected per village and all its HHs visited for data collection. Data were collected by trained and supervised surveyors from the immunization card, community immunization register, and questionnaire administered to parents of children living in the village. Main data collected included the immunization status and timing regarding BCG, polio zero, DPT-Hi+Hb1, DPT-Hi+Hb2, and DPT-Hi+Hb3 and sociodemographic characteristics. The sampling and implementation process of the surveys were similar but independent [1]. The surveys were conducted by independent survey teams different from the team in charge of implementation of the intervention under investigation.

The primary outcome is the timeliness of documented immunization of children, defined as the proportion of children aged <5 years with documented BCG vaccination status administered within the first month of life.

Secondary outcomes include the documented completeness of general EPI vaccination of children, defined as the proportion of children who started vaccination with BCG and who completed it by receiving the measles-rubella vaccine, as documented on the immunization card, and documented completeness of specific immunization of children, defined as the proportion of children who received DPT-Hi+Hb1 and who completed pentavalent vaccination doses by receiving the DPT-Hi+Hb3 vaccine, as documented on the immunization card. In addition, we will assess the timeliness of overall immunization of children, defined as the proportion of children completing all their EPI-recommended vaccines within the first year of life, as documented on the immunization card or not documented but tracked from caregiver memory, and completeness of overall immunization of children, defined as the proportion of children who started vaccination with BCG and completed it by receiving the measles-rubella vaccine, as documented on the immunization card or not documented but tracked from caregiver memory. Documented coverage of child immunization is defined as the proportion of children who will have received DPT-Hi+Hb3, as documented on the immunization card, and overall coverage of child immunization is defined as the proportion of children who have received DPT-Hi+Hb3, as documented on the immunization card or tracked from caregiver memory. We will also assess the documented recruitment rate, defined as the proportion of children starting vaccination with BCG, as documented on the immunization card, and the overall recruitment rate, defined as the proportion of children starting vaccination with BCG, as documented on the immunization card or tracked from their mother’s memory.

The effects of the intervention will be assessed by comparing completeness, timeliness, and coverage estimated from the intervention and control groups.

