### Study Period

This study was planned for a period of 18 months (from May 2018 to October 2019).

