### Sample Size Estimate

Using Stata software version 16.1 IC (StataCorp LLC, College Station, TX), the minimum required number of children to test the intervention was estimated at 20 children aged <5 years per cluster in at least 23 clusters of the control group and 20 in the intervention group. The estimate assumes between-cluster coefficients of variation of 0.38 and 0.19 in the control and intervention groups, respectively (estimated from baseline surveys in clusters assigned to each group), to reach 20 children who were <5 years old per cluster in each group, with assumptions that the proportion of children <5 years old vaccinated in the first month of life will remain at 20.5% (293/1430) based on a survey conducted in the targeted area prior to the intervention [1] and that an α error of .05 and 90% power will detect a 10% increase with the intervention in the proportion of children <5 years old vaccinated with BCG in the first month of their life. The estimate was guided by the method of estimating randomized controlled cluster trials proposed by Batistatou et al [15]. We adjusted to 32 clusters of at least 20 children per study group assuming 10% of the targeted children could not be reached (nonresponse and absence during the survey week) and in order to secure sufficient power to prevent cluster variation of estimated outcomes.

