### Data Analysis

The effect of the intervention will be assessed by estimating per study group and comparing (1) yearly immunization timeliness rates for BCG vaccine (proportion of children aged 0-59 months with evidence of vaccination in the first month of life) and measles-rubella vaccine (proportion of children aged 12-23 months with evidence of vaccination while 9-11 months old); (2) coverage of BCG (proportion of children aged 0-59 months who were vaccinated) and DPT-Hi+Hb1, DPT-Hi+Hb3, and measles-rubella (proportion of children aged 12-59 months who were vaccinated) vaccines; and (3) specific completeness (proportion of children who received DPT-Hi+Hb1 and DPT-Hi+Hb3 vaccines) and general completeness (proportion of children who received BCG and measles-rubella vaccines) while aged 12-59 months. Odds ratios for children being vaccinated, being vaccinated on time, and completing vaccination will be estimated and adjusted for the child’s guardians’ level of education and profession, type of population (seminomadic or sedentary), distance to the vaccinating health facility, and religion. The odds ratios will be controlled for variability using logistic regression random effects. The fixed parameters will include the outcome, study groups, child’s guardians’ level of education, type of population (seminomadic or sedentary), child’s guardians’ profession, distance to the vaccinating health facility, and religion, and the random effect will be controlled on the participants’ cluster. The analysis will be done based on the intention to treat principle [16]. Data will be collected using Open Data Kit (ODK)–designed forms on smartphones, verified in the field, and submitted to a secure server. Data will be monitored and cleaned in Microsoft Excel 2013 and analyzed using Stata version 16.1 IC.

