#### Procedures for the Interventions

In the intervention group, one community volunteer living in selected communities was selected with the help of the head of the CHC and trained to collect data monthly per HH in the same periodicity over 12 months: demographic movements of children aged 0-59 months (births, deaths, immigration, emigration, travel, and short-term visits) and immunization status regarding each of the EPI vaccines. They assessed immunization status of all children aged 0-59 months staying in the visited HH or visiting for a stay of at least one week, or who stayed there in the previous month and had left definitely or for less than a week. Data were recorded in a designated register. The filled pages of the register were snapped and sent to the CHC through WhatsApp to the team in charge of vaccination. From a rapid analysis of received data, the nurse communicated by SMS to the community volunteer the list of children eligible for the monthly immunization session. The community volunteers informed the parents of these children about the place and time of the immunization session and why they should not miss the immunization session. The community volunteers educated all pregnant women on the importance of delivering in a health facility to increase the chance of the newborn being vaccinated. For births occurring in a community on a date far from the planned community immunization session, the community volunteer encouraged the mother to carry the newborn to the closest vaccinating health facility to be vaccinated. The community volunteer of this group had to contact any nomadic group crossing his community to list all children aged 0-59 months and collect data on their vaccination status. If there were children that needed to be vaccinated, the community volunteer completed the register and sent the page to the nurse in charge of vaccination in the community. A vaccination session was organized to vaccinate these children in case the nomad group had to leave the village before the monthly immunization session. The community volunteer was asked to collect telephone contacts from all parents who planned to travel from his community with the child. The child's parent was called by phone to be reminded to have his or her child vaccinated by the competent team.

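### First-month BCG is analysed and powered in all children aged 0-59 months, although a 12-month intervention can change its timing only in those born during it or under one month old at its start

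*Protocol article*

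**What the plan says.** Outcomes Assessment gives the primary outcome as timeliness of documented immunization, "defined as the proportion of children aged <5 years with documented BCG vaccination status administered within the first month of life". Data Analysis repeats the denominator: "proportion of children aged 0-59 months with evidence of vaccination in the first month of life". Sample Size Estimate places the target effect in the same group, since the trial is to "detect a 10% increase with the intervention in the proportion of children <5 years old vaccinated with BCG in the first month" of life, starting from 20.5% (293/1430).

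Under Procedures for the Interventions, volunteers were "trained to collect data monthly per HH in the same periodicity over 12 months". The whole study was planned for "18 months (from May 2018 to October 2019"), so the intervention could not have run much longer.

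For measles-rubella timeliness, Data Analysis does use an age window: "proportion of children aged 12-23 months with evidence of vaccination while 9-11 months old". No such window, and no birth-date limit, is attached to BCG. One secondary outcome, "the proportion of children completing all their EPI-recommended vaccines within the first year of life", also has no age limit.

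**The concern.** A child either had BCG by one month of age or did not, and no later home visit or catch-up session alters that date. A child well over one year old at an endline survey held at month 12 had passed the window before the first visit. Such children bring only pre-intervention history into both arms. They pull the arm difference towards zero, and the analysis gives them full weight.

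The sample size carries the same feature. It asks for a 10-point rise in a group of whom most cannot have been vaccinated any earlier because of the trial. At stake is the primary conclusion: an intervention that clearly helps newborns could be reported as having no detectable effect.

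**Working it through.** **Inputs from Sample Size Estimate.** Control rate p0 = 0.205; target p1 = 0.305 (the 10% read as points, because a relative 10% would need about 620 clusters per arm); between-cluster coefficients of variation k0 = 0.38 and k1 = 0.19; m = 20 children per cluster, or 18 after 10% non-response; 32 clusters per arm adopted; alpha 0.05, taken as two-sided.

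**Assumptions not in the article.** Ages uniform over 0-59 months and the endline survey at month 12. The share born during the intervention is then f = 12/60 = 20%. Adding infants still under one month old at the start gives 13/60 = 21.7%. A range of 15-25% is carried throughout.

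**Formulas.** Variance of a cluster proportion: v = p(1-p)/m + (k·p)². SE = √[(v0 + v1)/32]. Power = Φ(d/SE - 1.96).

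**Step 1: the plan's own power.**
- v0 = 0.205×0.795/20 + (0.38×0.205)² = 0.00815 + 0.00607 = 0.01422.
- v1 = 0.305×0.695/20 + (0.19×0.305)² = 0.01060 + 0.00336 = 0.01396.
- SE = √(0.02817/32) = 0.0297, so power = Φ(0.10/0.0297 - 1.96) = 92%. With m = 18 it is 90%.

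The 90% claim therefore holds at the adopted size for a 10-point rise in all under-fives. The stated minimum of 23 and 20 clusters does not reproduce: the same formula needs 29.6 per arm, and 23/20 gives about 79% power. That is a separate matter, and nothing below depends on it.

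**Step 2: what the 10 points imply.** Overall rise = f × rise in exposed births, so the required rise is 0.10/f.
- f = 20%: 50 points, that is 20.5% to 70.5%.
- f = 15%: 67 points.
- f = 25%: 40 points.

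With f = 20%, timely BCG in every exposed birth would bring the overall rate only to 0.205 + 0.20×0.795 = 36.4%.

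**Step 3: power for a given true gain in exposed births.** The full denominator uses m = 20 and effect f·d. The restricted set uses m = 20f (3, 4 or 5 per cluster) and effect d, with the all-age 20.5% and both coefficients of variation carried over.

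| True gain in exposed births | Overall rise (f = 20%) | Power, all 0-59 months | Power, exposed births only |
|---|---|---|---|
| 10 points | 2 points | 11% | 42% |
| 20 points | 4 points | 29% | 92% |
| 30 points | 6 points | 55% | >99% |

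For the 20-point row, f = 15% gives 19% versus 84%, and f = 25% gives 42% versus 96%.

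**Step 4: detectable difference in the restricted set (90% power, 32 clusters per arm).**
- m = 4: 19.2 points, or 20.8 if k = 0.38 in both arms.
- Removing infants under one month leaves 4×11/12 = 3.7 per cluster: 20.0 and 21.6 points. Hence roughly 19-22.
- m = 5 to m = 3, across both choices of k: 17.3 to 23.7 points, hence about 17-24.

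**The case against.** A reader might infer that the 90% power claim is false. It is not: for the quantity that the article names, the adopted size delivers it (Step 1). What is missing is any statement or defence of the effect this implies in newborns.

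A reader might also take it as fact that 80% of the children cannot respond. The article does not support that, for two reasons. The share rests on an assumed age distribution. And the outcome is *documented* timeliness: surveyors also read the community register, which was used to trace status when a card was lost, and the Discussion expects the two registers to improve documented timeliness. An older child's recorded result can therefore move. That objection stands as far as it goes, but such a shift would be a recording difference, not earlier vaccination, and mixing it into the primary outcome makes the result harder to interpret.

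Data Analysis speaks of *yearly* timeliness rates, which might be thought to imply birth cohorts. No cohort is named, and the definition that follows fixes 0-59 months.

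Some caution on the figures is fair. The 20.5% and the coefficients of variation describe all under-fives, not infants. The planned analysis reports odds ratios, whereas the dilution factor above applies to risk differences. Even restricted, the trial has only about 42% power for a 10-point gain. Dilution also biases towards no effect and does not create false positives.

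The strongest objection concerns timing. The Results section says that data collection was complete by January 2020, so changing the primary analysis set now is a change after data collection. That is a real cost and must be disclosed.

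**Conclusion.** The concern holds. The denominator is fixed as all under-fives in the outcome, the analysis and the sample size, while the intervention could alter the date of first-month BCG only in children born during it or under one month old when it began. With about 20% exposed (15-25%), the planned 10-point rise needs about 50 points (40-67) in those births, and a true 20-point gain has about 29% power (19-42%), against about 92% (84-96%) in exposed births alone.

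These sizes depend on uniform ages, an endline survey at month 12, and the all-age rate and coefficients of variation carrying over to infants. The direction does not depend on them. At a midline survey the exposed share would be smaller still. Children who moved between communities blur the cut slightly.

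**What to change.** Before the arms are compared, and by a dated, disclosed amendment:

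- Define the BCG timeliness analysis set as endline children born on or after the intervention start in their community and aged at least 1 month at survey. Control communities have no start of their own, so name the date that applies to them, for example that of the paired community.
- Report the registered 0-59 month proportion alongside it.
- Restate the detectable difference: roughly 19-22 points at 90% power with about 4 eligible children per cluster and 32 clusters per arm (about 17-24 points for 5 to 3 per cluster), with the carried-over rate and coefficients of variation given as assumptions.
- For the secondary outcome on completing all vaccines in the first year, state an age limit, but do not present 12-23 months as a full remedy. A child aged 23 months at endline was about 11 months old when the intervention began, and most of that age band spent much of their first year before it.

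No new data should be needed, since BCG timing was collected and age is required for the outcome anyway. The costs are fewer children, a less favourable detectable difference, and a change to the primary analysis set after data collection. The amendment should say whether any comparison of the arms had already been seen.

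### First-year timeliness of the whole schedule accepts undated caregiver memory and, alone among the memory-accepting outcomes, has no documented counterpart

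*Protocol article*

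**What the plan says.** Outcomes Assessment lists a secondary outcome, "timeliness of overall immunization of children, defined as the proportion of children completing all their EPI-recommended vaccines within the first year of life". The evidence accepted is the card or, failing that, recall: "within the first year of life, as documented on the immunization card or not documented but tracked from caregiver memory". No age range is attached to it.

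The same section gives card-based versions of the other concepts: "documented completeness of general EPI vaccination of children", "Documented coverage of child immunization is defined as the proportion of children who will have received DPT-Hi+Hb3, as documented on the immunization card" and "documented recruitment rate, defined as the proportion of children starting vaccination with BCG, as documented on the immunization card". Each has a second version that also accepts memory. Specific completeness (first to third pentavalent dose) is card-only.

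"The primary outcome is the timeliness of documented immunization of children", but it concerns one vaccine and one month: "proportion of children aged <5 years with documented BCG vaccination status administered within the first month of life". Data Analysis adds timeliness of measles-rubella at 9 to 11 months among children aged 12 to 23 months, resting on evidence of vaccination that is not specified as card-only.

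Under Procedures for the Interventions, volunteers in the intervention group were "trained to collect data monthly per HH in the same periodicity over 12 months". They recorded vaccination status, and they told parents of eligible children when and where the session was and why it mattered. The Control section describes routine sessions only. Outcomes Assessment states that survey teams were separate from those implementing the intervention.

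**The concern.** Whether a child was ever vaccinated can reasonably be asked of a caregiver without a card. Whether a whole series was finished before the first birthday is a question about dates, and recall is much weaker evidence for that. Children up to 59 months are eligible, so for the oldest the first birthday lies almost four years back.

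If recall error were the same in both arms, it would mainly blur the comparison. Here a year of monthly conversations about vaccination takes place in one arm only, so the error may differ by arm. Timeliness is one of the trial's three stated aims, and this is its only outcome for timeliness of the whole schedule. As it stands, a difference (or the lack of one) could not be separated from a difference in recall, because no documented version is defined to set beside it.

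**Working it through.** **Step 1: pair the outcomes (Outcomes Assessment).**

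| Concept | Card version | Card-or-memory version |
|---|---|---|
| General completeness (BCG to measles-rubella) | yes | yes |
| Specific completeness (pentavalent 1 to 3) | yes | no |
| Coverage (pentavalent 3) | yes | yes |
| Recruitment rate (BCG) | yes | yes |
| All vaccines within first year | **no** | yes |

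Four outcomes accept memory, and only the last lacks a card version. The missing version of specific completeness is the memory one, so it raises no recall problem.

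**Step 2: can another measure stand in?** The primary outcome covers BCG in the first month, a different vaccine and window. Measles-rubella at 9 to 11 months is closer, since it falls late in the schedule and in a narrow age band. It is still one vaccine, and its evidence source is not defined.

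**Step 3: could error differ by arm?** Monthly household contact about vaccination is described for one arm only. It could push error either way:
- Upward: caregivers may over-report. The Discussion says children aged 12 to 59 months could receive missed doses; a late catch-up dose may be remembered as part of a schedule finished on time.
- Downward: repeated review of status may make recall more accurate and reduce false on-time answers.

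**Step 4: illustrate the size.** The plan states no figure for this, so there is none to reproduce. Assume no true effect, with the same true on-time share *T* and the same share without a card *u* in both arms. Let Δf be the between-arm difference in the probability that a child who was not on time is recalled as on time. Then

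spurious difference = *u* × (1 − *T*) × Δf.

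The chance of a two-sided 5% rejection uses 32 clusters per arm (Sample Size Estimate). It assumes *m* = 16 assessable children per cluster, a between-cluster coefficient of variation *k* = 0.25, and variance per cluster *V* = *p*(1 − *p*)/*m* + *k*²*p*².

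Worked case, *T* = 0.20, *u* = 0.40, Δf = 0.10:
- Spurious difference: 0.40 × 0.80 × 0.10 = 0.032.
- *V* at 0.200: 0.0100 + 0.0025 = 0.0125. *V* at 0.232: 0.0111 + 0.0034 = 0.0145.
- Standard error: √(0.0270/32) = 0.029, so *z* = 1.10.
- Chance of rejection: Φ(1.10 − 1.96), about 20%.

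Spurious points, with chance of a significant result in brackets:

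| *T* | *u* | Δf = 5 points | 10 | 20 | 30 |
|---|---|---|---|---|---|
| 0.20 | 0.40 | 1.6 (9%) | 3.2 (20%) | 6.4 (57%) | 9.6 (87%) |
| 0.40 | 0.40 | 1.2 (6%) | 2.4 (9%) | 4.8 (22%) | 7.2 (41%) |
| 0.60 | 0.20 | 0.4 (5%) | 0.8 (5%) | 1.6 (6%) | 2.4 (8%) |

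The most extreme combination tried (*T* = 0.20, *u* = 0.60, Δf = 30 points) gives 14.4 points. If Δf is negative, the same sizes apply with the sign reversed, and a true benefit would be masked.

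**Step 5: apply the same test to card-only scoring.** If every child without a readable card counts as not on time, and card holding is unrelated to timeliness, the spurious difference is *T* × (arm difference in card availability). With *T* = 0.40 and a 10-point difference (both assumed), 0.40 × 10 = 4 points. The Discussion itself expects the two registers to improve documented timeliness, so this is not remote.

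**The case against.** The strongest reply is that the reach is small. This is one secondary outcome among several; the primary outcome is documented; and Data Analysis has a measles-rubella timeliness measure in young children. Independent survey teams reduce interviewer bias. Outcomes Assessment says timing as well as status was collected, from card, community register and parent questionnaire, and how recall was elicited may be set out in the full protocol. Every input to the size is assumed. A card-only version brings its own arm-dependent bias.

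Much of this stands. The primary conclusion is untouched, the size is unknown, and card-only scoring is no clean replacement. It also cannot be said that recall yields no timing information at all; the point is only that the definition lets undocumented recall settle a question of dates. What does not answer the concern: independent interviewers do not change what caregivers remember, and neither single-vaccine measure covers the whole schedule.

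A reader might go further and infer that the definition will create a false benefit for the intervention. The documents do not support that. Contact may sharpen recall as well as inflate it, and registers used when cards are lost may leave different shares resting on memory in the two arms.

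**Conclusion.** The point holds as a gap in one secondary definition. First-year timeliness of all vaccines accepts undocumented memory and is the only memory-accepting outcome without a documented version, in a trial where one arm alone has monthly household contact about vaccination. Recall error that differs by arm is plausible and could produce or mask a difference.

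Its size rests wholly on assumptions about card retention, true timeliness and recall, none of which the article gives. The illustrations run from 0.4 points with no real inflation of the error rate to 14.4 points. Setting these beside the 10% increase in the sample size calculation is only a rough yardstick, since that figure belongs to the BCG outcome.

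Two stronger inferences should be resisted: that the trial's main timeliness result is compromised (it is card-based), and that card-only evidence should simply replace memory (Step 5 shows why not).

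**What to change.** - Add a documented version of first-year timeliness, based on dated card records, in children aged at least 12 months at survey. Report it beside the card-or-memory version in the same age group.
- Show by arm the share of children with a readable card and the share judged from memory. State how community register entries are classed, since the outcome definition names only card and memory.
- Base any claim of improved first-year timeliness on agreement of the two versions. Let memory-only evidence stand in its own right only for the vaccinated yes/no outcomes, which already have documented partners.

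The cost is low: a definition and one table. The article reports analysis as ongoing, so no new fieldwork is needed provided card dates were captured for every vaccine in the schedule. This should be confirmed, because the list of main data in Outcomes Assessment stops at the third pentavalent dose, although Data Analysis uses measles-rubella timing. The change should be disclosed as made after data collection.

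The downside is that the documented rate will be lower and can itself differ by arm through card retention or better record-keeping. That is why both versions and the evidence source by arm are needed.
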